**8.2 Final Inclusion**

The final inclusion will be determined after the bacteriological result of the BAL becomes available. A sheet for final inclusion, including bacteriological information and a copy of the informed consent is faxed to the principal investigator.

**8.3 Randomisation**

Is carried out in the final inclusion. It will be performed by the main investigator centre using a pre-defined centre randomization table. The assigned treatment arm is communicated by fax between 8 a.m. and 12 p.m., Monday to Friday and at the latest by D5.

1. **Methodology**

- **Pre-inclusion**
- verification of the criteria for inclusion (except bacteriological data) and exclusion
- realization of the BAL
- realization of 3 blood cultures
- simplified acute physiologic score: SAPSIIS II (Appendix VIII)(Appendix IX) Mc Cabbe score - score of organ failure (ODIN: Appendix X)
- -score of organ failure related to sepsis (SOFA: Appendix V)
- **Inclusion**
- verification of the bacteriological criteria for inclusion.
- **D0 of treatment**
- SAPS II (Appendix VIII) score
- score of organ failure (ODIN: Appendix X)
- score of organ failure related to sepsis (SOFA: Appendix V)
- **D1 of treatment**
- SAPS II (Appendix VIII) score
- score of organ failure (ODIN: Appendix X)
- score of organl failure related to sepsis (SOFA: Appendix V)
- rectal swabs
- **D4 of treatment**
- **decrease of dosages of beta-lactam - interim evaluation**

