**3. Objectives of the study**

**This is a prospective, randomized, open, multi-center study.**

**3.1 Primary Objective**

To show that antibiotic therapy of 8 or 15 days is equivalent in terms of clinical cure rates in the treatment of early onset nosocomial pulmonary infection in patients receiving mechanical ventilation.

- 1. **Secondary Objective**

**. Study of nosocomial infections:** assessing the influence of the duration of antibiotic treatment on the rate of potentially fatal pulmonary and extra-pulmonary infection (definition of nosocomial infections: annex XIII).

- **Study of bacterial Ecology:** research of changes in the flora of the gut under treatment and analysis of pathological samples (antibiotic resistance phenotypes +/- genotypes).

**. Economic Survey:** analyze the costs related to the treatment of nosocomial pneumonia and its complications in the two study groups.

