**5.2 Treatment**

All patients included in the study will be treated by a combination of antibiotics during the first 5 days (Beta-lactam + Aminoglycoside), then by monotherapy (Beta-lactam alone) for 3 or 10 days according to the group. The beta-lactam antibiotics will be administered in high doses during the first 3 days of treatment. Aminoglycosides will be administered as a single daily dose, with a loading dose administered on the first day of treatment. The patient will remain hospitalized (intensive care units or other units) for the duration of the treatment.

Definition :

- J0 = introduction of treatment whatever the time is
- J1 = first full day of treatment
- J4 = decrease in the dose of beta-lactam antibiotics, after 3 full days of treatment with high dose antibiotics; intermediate evaluation will be performed
- J6 = Stop aminoglycosides, after 5 full days of treatment
- J9 = Stop beta-lactam antibiotics in the "short" arm.
- J16 = Stop of the beta-lactam antibiotics in the "long" arm.
- J21 = Final evaluation.

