**7.2.1 Failure ;**

- Death for what ever reason during the protocol

- Initial clinical worsening judged after D3 of treatment:

septic shock (Appendix IV) or "sepsis syndrome" (Score of organ failure related to sepsis: SOFA Appendix V) without another documented infection - increase in the score of organ failure (increase in SOFA score by 2 points or more) with identification of the same microorganism at a new BAL

- Persistence or increase of all signs of pulmonary infection after D3 of treatment:

- temperature > 38.5° or < 36 °

- > 12000 WBC / mm3 or < 5000 / mm3

- purulent bronchial secretions

- absence of pulmonary radiological improvement and persistence of the original microorganism in the BAL

- A need to change the initial antibiotic for treatment intolerance (Appendix VI)

If failure is diagnosed, regardless of the day (After D3 of treatment), the patient is assessed as failure in the final evaluation at D21.

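### Section 8.3 releases the treatment arm by D5, although the arms do not differ until D9 and failures called in between are final

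*Protocol*

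**What the plan says.** Section 5.2 writes J where section 8.3 writes D. The days are the same, and D is used below outside quotes.

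- **Design (section 3):** "This is a prospective, randomized, open, multi-center study". No blinded assessor is described.
- **Treatment (5.2):** five days of combination therapy, "then by monotherapy (Beta-lactam alone) for 3 or 10 days according to the group". The D4 dose reduction and the D6 aminoglycoside stop apply to both arms. The arms part at "J9 = Stop beta-lactam antibiotics in the 'short' arm", against "J16 = Stop of the beta-lactam antibiotics in the 'long' arm".
- **Inclusion (8.2):** "The final inclusion will be determined after the bacteriological result of the BAL becomes available". Randomisation takes place at that step (8.3).
- **Release of the arm (8.3):** "The assigned treatment arm is communicated by fax between 8 a.m. and 12 p.m., Monday to Friday and at the latest by D5". No earliest day and no reason for D5 are given.
- **Failure (7.2.1):** "If failure is diagnosed, regardless of the day (After D3 of treatment), the patient is assessed as failure in the final evaluation at D21".

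**The concern.** Up to and including D8 the assigned treatment is the same for everyone. Any difference between arms in failures called by then is chance, or the behaviour of people who know the arm. The protocol lets such calls be made, makes them final, and tells the site the arm before the site needs it.

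Three decisions in that window are open to influence:

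- whether to repeat a BAL, since the persistence criterion can only be met if someone looks for the original organism;
- how to judge secretions and the chest X-ray as parts of that combined criterion;
- whether to record a change of the initial antibiotic for intolerance. Section 9.3 leaves continuation after an adverse event to the investigator's discretion, and the Appendix XII form carries the arm beside the question on relationship to treatment.

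A clinician who knows that treatment ends at D9 may look harder on D6 to D8 than one who knows that it runs to D16. Equivalence is judged against 10 points (11.2), so even a small net shift would count.

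**Working it through.** **1. Day of divergence (5.2, D1 = first full day).** Short arm: 5 + 3 = 8 full days, so stop at D9. Long arm: 5 + 10 = 15 full days, so stop at D16. Both reproduce the protocol's own days.

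**2. Exposed days.** Failure is possible after D3, so the failure-eligible days before divergence are D4 to D8, five days. If the fax is sent on D5, the arm is known on D5 once it arrives and throughout D6 to D8. If it is sent earlier, more days are affected. Under 5.1 some patients start treatment only after the BAL result, so their arm could be released around D0.

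**3. How long release could wait.** Faxes go Monday to Friday. The table counts back from D9 to the latest weekday slot under each rule (public holidays ignored).

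| D9 falls on | D5 falls on | Latest slot now (on or before D5) | Latest slot on or before D8 | Days gained |
|---|---|---|---|---|
| Mon | Thu | D5 | D6 (Fri) | 1 |
| Tue | Fri | D5 | D8 (Mon) | 3 |
| Wed | Sat | D4 (Fri) | D8 (Tue) | 4 |
| Thu | Sun | D3 (Fri) | D8 (Wed) | 5 |
| Fri | Mon | D5 | D8 (Thu) | 3 |
| Sat | Tue | D5 | D8 (Fri) | 3 |
| Sun | Wed | D5 | D7 (Fri) | 2 |

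The gain is larger where the fax now goes out before its deadline.

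**4. Which failure routes are open to judgement (7.2.1).**

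| Route | What it needs | Room for influence |
|---|---|---|
| Death | any cause | little |
| Worsening | septic shock, or sepsis syndrome or SOFA rise; same organism on a new BAL is also named | limited |
| Persistence | all signs together, including the original organism on BAL | decision to re-sample; reading of secretions and X-ray |
| Antibiotic change | intolerance only (Appendix VI) | decision to change and how to record it |

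**5. Sensitivity to a shift (illustration, not an estimate).** The documents give no rate of biased calls. Assume the last row of the 11.2 table: cure p = 0.80, n = 140 per group, margin 0.10. Read its two risks as one-sided alpha 0.10 and beta 0.20; the column symbols are lost. With short-arm cure q and SE = √[p(1−p)/n + q(1−q)/n], power = Φ[(0.10 − (p − q))/SE − 1.282].

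- No shift, q = 0.80: SE = 0.0478, power 0.79.
- 2 points of extra failure calls in the short arm, q = 0.78: SE = 0.0487, power 0.64.
- 5 points, q = 0.75: SE = 0.0498, power 0.39.

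In the other direction, with a true deficit of 10 points and an apparent shift of 2 or 5 points in favour of the short arm (q = 0.72 or 0.75), the chance of wrongly accepting equivalence rises from 0.10 to 0.19 or 0.39.

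**The case against.** The passages do not contradict each other, and the trial is openly declared unblinded. Cure is assessed at D21, long after the arm must be known, and the only scheduled evaluation before D9 is at D4, which can precede the fax. Most early failures cannot be produced by behaviour alone. Purulent secretions or an unimproved X-ray do not make a failure without the other signs and the original organism on BAL. A change of antibiotic for a new infection is permitted (5.5) and is not a failure. A new BAL that is sterile or grows a different organism leaves the patient evaluable at D21 (7.3). All of this stands, and it limits the reach of the point.

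D5 may also have a purpose. Consent may be obtained during the first three days (6.1), a copy must accompany final inclusion (8.2), and faxes go on weekdays only, so a D3 on a Saturday leads to Monday, D5. A reader might infer that early release has no reason at all. The documents show only that none is stated. But a deadline for completing inclusion and drawing the arm does not require the site to be told the arm on the same day.

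A last-slot release leaves less reserve. If a fax is missed, a short-arm patient could be treated past D9, which would make the arms more alike. That cost is real and has to be managed.

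**Conclusion.** The point holds as a cheap improvement. The arm is released 1 to 5 days before the last usable fax slot, even when the site is told at the deadline, and irreversible failures can be called in that window. The size and net direction of any bias are unknown. The shifts of 2 to 5 points used above are assumptions that show sensitivity only.

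Two stronger readings are tempting and are not supported:

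- *That sites could be kept fully blind for the first eight days.* With weekday faxing the arm is still known from D6 when D9 is a Monday, from D7 when it is a Sunday, and otherwise from the morning of D8.
- *That dilution by early failures measures this defect.* If 5%, 10% or 15% of patients failed before D9 (assumed), a deficit of 10/(1 − f) = 10.5, 11.1 or 11.8 points among the rest would show as 10 overall. That holds whatever day the fax is sent, and the 10-point limit in 11.2 is set on the overall cure rate.

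Knowledge of the arm from D9 onward remains whatever is done here.

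**What to change.** In 8.3, keep registration and the draw at final inclusion. Hold the allocation at the coordinating centre and fax it on the last weekday morning on or before D8: D8 if D9 falls Tuesday to Saturday, D7 if Sunday, D6 if Monday. Require the site to confirm receipt, so that a missed fax is noticed. The arm box on the Appendix XII form would stay blank for events declared before release.

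In the statistical analysis section, add one supportive comparison, by randomised arm, in patients alive and not failed at D9. Describe this subset as largely, not wholly, protected from knowledge of the arm. The intention-to-treat comparison stays primary.

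Cost: two edits and one extra analysis, with no added patients, visits or procedures and no change to any treatment rule. The downside is shorter notice to wards and less reserve if a fax is missed.

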**. D6 of Treatment**

- Stop Aminoglycoside

- **D9 of treatment**
- rectal swabs
- interim evaluation of healing
- **D16 of treatment**
- rectal swabs
- interim evaluation of healing
- **D leave intensive care or hospital if  21 days** : intermediate evaluation of healing

**D21 : Final evaluation = failure or cure**

**For all days preceding the final assessment, patients will be monitored according to clinical and biological criteria. All intercurrent events will be taken into account (lung infections, other infections, shock, toxic manifestations relating to the treatment...) (Appendix VII)**

1. **Legal dispositions**

The test is conducted under the responsibility of the investigator, under the French research regulation.

**9.1 Comité Consultatif de Protection des Personnes se prêtant à la Recherche Biomédicale (CCPPRB) : (Ethical and research committee)**

Before performing the study, the principal investigator will submit the project for the opinion of the CCPPRB. The study will begin only after being deemed favourable and without reservations from the Committee and after applying for insurance. The investigator will inform the CCPPRB of any subsequent amendments and any serious or unexpected intercurrent event occurring during the study that would affect the safety of subjects or the conduct of the study. In this case, information will be issued to all investigators. Each collected informed consent (Appendix XI) will be presented in a sealed envelope.

**9.2 Directors of intensive care unit and Director’s hospital Agreement :**

Their agreement depends on the participation of an investigator centre.

**9.3 Side effects :**

It is the responsibility of investigators to document all intercurrents events occurring during the study. Intercurrents events include drug interactions or organic diseases that emerge during the study, regardless of the relationship with the treatment received. Antibiotics used in the test have known pharmacokinetic characteristics and potential adverse effects. All measures must be taken to define the relationship of causation between the treatment and intercurrent event.

In the event of a death, a statement must be made to the principal investigator who will inform the regulatory agency within 24 hours (from Monday to Friday). Serious events (annex VI) will be the subject of a declaration to the pharmacovigilance centre connected to the investigator centre (Act of 24 May 1984) (Declaration of serious intercurrent event worksheet: Appendix XII). For accountability to the studied treatments, the investigator should inform the lead investigator, who will take care of the regulatory agency information. All treatments adapted to the state of the patient will be implemented to ensure the support of intercurrent event. The continuation of the ongoing antibiotic treatment is left to the discretion of the investigator in charge of the patient.

**10. Secondary objectives**

For each of the two groups the following studies will be conducted:

**10.1 Study of nosocomial superinfections**

**Objective:** to evaluate the influence of the duration of antibiotic treatment on the prevalence of fatal pulmonary and extra-pulmonary infections (definitions of nosocomial infections: Appendix XIII).

**Method:** Consideration of all the infectious intercurrents events observed while the patient is in an intensive care unit, for a maximum period of 3 weeks.

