**Appendix XIII : Nosocomial Superinfection definitions**

- Bacteremia: 1 positive blood culture or 2 positive blood cultures if Staphylococcus épidermidis
- catheter: cultures of the tip of the catheter > 10 3 cfu /ml
- Urine : cultures >10 5 cfu / ml and Neutrophils > 10 / field
- Pulmonary: BAL sample culture >10 4 ufc/ml
- Sinusitis: sinus puncture positive
- Surgical wounds: growth of bacteria on local sample

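### Superinfections are counted only during ICU stay, so the arms can be compared over unequal exposure, and the outcome is worded three different ways

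*Protocol*

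**What the plan says.** **Counting window.** The method in section 10.1 is "Consideration of all the infectious intercurrents events observed while the patient is in an intensive care unit, for a maximum period of 3 weeks". It does not say on which day the three weeks begin, and it gives no person-time denominator.

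**Where patients are.** Section 5.2 allows treatment outside the ICU: "The patient will remain hospitalized (intensive care units or other units) for the duration of the treatment". The same section stops the beta-lactam at J9 in the short arm and J16 in the long arm. Section 7.2.2 has cure rules for patients already at home by D21.

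**What is recorded.** The D21 entry that closes section 8 states: "For all days preceding the final assessment, patients will be monitored according to clinical and biological criteria". It asks for all intercurrent events, infections included. Section 9.3 makes investigators document every intercurrent event during the study, and section 10.3 costs the pneumonia and its complications from D0 to D21. None of these stops at ICU discharge.

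**What the outcome is.** The secondary objective in section 3 speaks of "the rate of potentially fatal pulmonary and extra-pulmonary infection". The objective in section 10.1 speaks of "the prevalence of fatal pulmonary and extra-pulmonary infections". The method in section 10.1 takes all infectious events. Both objectives point to Appendix XIII, which defines infection by site, mostly by culture, for example "Pulmonary: BAL sample culture >10 4 ufc/ml".

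**The concern.** Leaving the ICU is a post-randomisation event. The trial is open, so the arm is known when discharge is decided, and the introduction itself says that nosocomial pneumonia lengthens stay in many ventilated patients. If antibiotic duration changes ICU stay in either direction, the arm that stays longer collects more countable infections at the same daily risk. A difference in superinfections could then appear, shrink or reverse because of the window alone. Apart from bias, infections that arise on the ward or at home before D21 do not reach the analysis meant to capture them.

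The three wordings add a second problem. Fatal infections, potentially fatal infections and all infections are different sets, and the cited definitions give no rule for picking out the first two.

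**Working it through.** **No plan figure to reproduce.** The protocol gives no expected rate, sample size or power for this outcome. What follows is an illustration on assumed inputs.

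**Inputs.**
- Daily hazard h of a countable superinfection: not in the protocol; assumed to be 1, 2 or 3% per day and *the same in both arms*.
- Mean ICU days d: not in the protocol; assumed to be 14 in one arm and 14, 12 or 10 in the other.
- Upper limit of 21 days: section 10.1.

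**Formula.** Expected proportion with an event = 1 − exp(−h × d).

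Worked example at h = 0.02: 14 days gives 1 − exp(−0.28) = 24.4%; 12 days gives 1 − exp(−0.24) = 21.3%. The difference is 3.1 points with no true effect on daily risk.

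| h per day | 14 days | 12 days | difference | 10 days | difference from 14 |
|---|---|---|---|---|---|
| 1% | 13.1% | 11.3% | 1.8 | 9.5% | 3.5 |
| 2% | 24.4% | 21.3% | 3.1 | 18.1% | 6.3 |
| 3% | 34.3% | 30.2% | 4.1 | 25.9% | 8.4 |

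Differences are in percentage points, taken before rounding. With 14 days in both arms the difference is 0 at every hazard.

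**A common window.** Over 21 days in both arms, the expected proportion among patients alive throughout is 18.9%, 34.3% and 46.7% at 1, 2 and 3% per day. The difference is 0 whatever the ICU stay. A window from randomisation to D21 is shorter, but it is alike in both arms, so the difference is again 0.

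**Would counting in any hospital unit be enough?** No. Section 5.2 ties hospital stay to treatment length. In the extreme case where patients go home when treatment stops, at 2% per day: 1 − exp(−0.02 × 9) = 16.5% against 1 − exp(−0.02 × 16) = 27.4%, an artefact of about 11 points. That is larger than any value in the table.

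**Wording side by side.**

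| Place | Events meant |
|---|---|
| Section 3, secondary objective | potentially fatal |
| Section 10.1, objective | fatal |
| Section 10.1, method | all |
| Appendix XIII (cited by both objectives) | site-based criteria, no fatality criterion |

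**The case against.** The strongest reply has four parts.

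1. *Nothing shows that ICU stay will differ.* A reader might infer that the arms are bound to be compared over unequal exposure. The documents do not support that: the planned regimens are the same until the short arm stops at J9, and no ICU stay by arm is given. This stands. The defect is that the window allows the bias.

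2. *ICU-only counting is defensible.* Several Appendix XIII criteria need BAL, a catheter tip or a sinus puncture, and section 5.5 requires BAL before an antibiotic change for new lung infection only in intubated patients. Detection is more even inside the ICU. This is a good reason to keep an ICU measure, but not to make an ICU-only count the sole measure.

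3. *The denominator may be in a statistical analysis plan that is not shown.* Section 3 does say rate, and a rate per ICU-day would remove much of the exposure problem. This also stands in part. However, the ICU limit and the three wordings are fixed in the protocol, and no denominator brings back infections that arise after ICU discharge.

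4. *The wording is a detail.* 'Fatal' may be a translation slip, and the section heading and Appendix XIII both point to superinfections in general. That is plausible, but the current text still gives three outcomes and needs reconciling.

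Two further readings go too far. One is that later infections are lost to the trial: the protocol requires them to be recorded, and only this outcome leaves them out. The other is that fewer superinfections are the main safety case for short treatment: section 2.2 names adverse effects, resistance, colonisation by multi-resistant bacteria and cost.

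**Conclusion.** The point holds as a weakness of one secondary outcome. Section 10.1 ties the count to a period that follows randomisation and may respond to treatment. It also disagrees with the recording rules at the end of section 8 and in section 9.3, and with the D0 to D21 window of section 10.3. The outcome has three incompatible descriptions and no criterion for two of them.

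The possible artefact runs from zero, if ICU stay is equal, to 1.8–4.1 points for a two-day difference and 3.5–8.4 points for a four-day difference. These figures rest on an assumed constant daily hazard of 1 to 3%, equal in both arms, and on assumed stays starting from 14 days. They show scale and are not forecasts; the direction depends on which arm stays longer. The loss of post-ICU infections does not depend on these assumptions. The primary D21 cure endpoint is not affected, so the change is advisable but not critical.

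**What to change.** - **One definition.** In sections 3 and 10.1, name the outcome as all Appendix XIII superinfections, and list the fatal ones separately.
- **One window.** Count from randomisation to D21 in both arms, wherever the patient is (ICU, ward or home), with death as a competing event. This also settles the unstated start of the three weeks. Do not limit the count to hospital days, for the reason shown in the working.
- **ICU measure alongside.** Report ICU-only incidence per 1000 ICU days as a secondary result.

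**Cost.** Low. The daily sheet in Appendix VII already records ICU, ward or home and secondary infections by site, so the change is mainly wording.

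**Downside.** Detection is weaker on the ward and weaker still at home, where section 7.2.2 names only a D21 telephone interview about new antibiotics for lung infection. Because the short arm can go home earlier, weak detection there could itself differ by arm. Events should therefore be shown by place of detection. Widening the call to any new infection would help, although an infection without a culture will usually not meet Appendix XIII and should be listed apart.
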